##### Example of adaptive prescription toileting (functional component)

1. Equipment

a) Electronic controls (e.g., clapper, motion detector)

b) Oxygen tank w/extra tubing/portable tank

c) Mobility Aid: walker, cane, crutch, wheelchair

d) Lift: Mobile (e.g. Hydraulic/Mechanical), Overhead

e) Gait belt

f) Sliding, transfer board

g) Bedside Commode

h) Urinal

i) Catheter with bag

j) Other: ___________________

2. Physical/spatial modifications

k) Change floor surface (replace floor, remove rugs or obstacles)

l) Add lighting (e.g., new fixtures, change curtains, night light)

m) Decrease glare

n) Change light controls (move switch)

o) Remove unnecessary objects: throw rug, shower curtain, towels, etc

p) Rearrange furniture or bathroom fixtures to create more space

q) Remove walls (e.g. closet) or add on to bathroom to create more space

r) Use a different toilet: commode chair, use another bathroom, add a new bathroom

s) Install new grab bars

t) Replace or move existing grab bars

u) Change toilet height: replace toilet, raised toilet seat, donut, safety frame, toilevator

v) Stabilize toilet

w) Other: ___________________

3. Adaptive methods

x) Use a urinal or different bathroom

y) Bed mobility method

z) Bed mobility training and practice

aa) Transfer method

bb) Transfer training and practice

cc) Stay within "triangle of efficiency"

dd) Catheterization

ee) Bowel program

ff) Prompted voiding

gg) Use diapers

hh) Other: ___________________

4. Energy conservation

ii) Take your time

jj) Go to the toilet more often, so you don't have to rush

kk) Use a nearby toilet: commode, different bathroom

ll) Prepare ahead (e.g., toilet paper near, other items for toileting, etc.)

mm) Adjust equipment before changing position

nn) Avoid transfers when tired

oo) Ask for help if you feel sick or especially tired

pp) Allow time for eyes to adjust to change in lighting

At the discretion of the teletherapist, a prn visit (televisit 4) is performed in the event that interval problems arise that cannot be addressed telephonically and that do not require medical evaluation at the hospital (e.g., a minor fall and the circumstances of which cannot be adequately addressed telephonically).

#### Telephone Intervention

There are a total of five telephone calls from the teletherapist to the participant. The first telephone call occurs during Week 2 (approximately 7-10 days after televisit 1). During the first call, the teletherapist establishes rapport with the participant by commending them on what they did appropriately and providing positive feedback on their performance as appropriate. The call allows for clarification of any concerns the teletherapist may have, reviewing the participant's current exercise program, discussing participant preferences and soliciting cooperation and input from the participant. Some preliminary treatment or exercise recommendations may be made at this time, if appropriate, and any potentially dangerous activities viewed on the videotape are discussed in detail with alternative strategies provided. If the videotaped evaluation shows that assistive technology or adaptive equipment is needed, the teletherapist asks the participant for permission to order relevant equipment through the VAMC.

If the IHMD was not set up in the home due to lack of an analog telephone line, the teletherapist uses the exercise dialogue from the IHMD to query the participant about exercise adherence. The teletherapist discusses impediments to participants performing exercises and engages the participant in troubleshooting ways to get around barriers in order to encourage adherence to the exercise program. The exercise dialogue enables flexibility such that participant needs drive the content of the call. This exercise dialogue was derived from recently published clinical trials that were used to promote improved physical activity [22,23]. Table 2 presents the contents of the 'Exercise Adherence Dialogue Response Form'.

**Table 2 T2:** Exercise adherence dialogue response form

	Teletherapist questions:	Responses:		
1.	In the last **WEEK**, has anything happened to your **PHYSICAL **health or in your life that we should know about that will prevent you from starting your exercise routine?	**Yes**	**No**	

2.	If response is **Yes**: "I am sorry to hear that. If you feel dizzy, have problems with your speech, eyesight, or increased weakness, you should call your doctor or 911."			

3.	Let's take a look at the exercise plan that we put together. Have you been able to follow this plan?	**Yes**	**No**	

4.	If answer is **Yes**, "That is great! Keep up the good work, and continue to exercise as often as you are able to do so."			

5.	If answer is **No**, go to question #28.			

6.	So, let us take a look at your **BALANCE ACTIVITIES**. In the past week, did you do the exercises we gave you?	**Yes**	**No**	**N/A**

7.	Exactly how many **TIMES **last week were you able to do the balance activity?	**Times**		

8.	Exactly how many **MINUTES **were you able to do the balance activity each time?	**Minutes**		

9.	So, let us take a look at your **STRENGTH ACTIVITES**. In the past week, did you do the exercises we gave you?	**Yes**	**No**	**N/A**

10.	Exactly how many **TIMES **last week were you able to do the strength activity?	**Times**		

11.	Exactly how many **MINUTES **were you able to do the balance activity each time?	**Minutes**		

12.	Please tell me what **EXERCISES **you have been able to do this week.			

	**Exercises for non-ambulatory/unable to stand independently:**			

13.	Did you do the **BRIDGING **exercise?	**Yes**	**No**	**N/A**

14.	Did you do the **LEG CROSSOVER **exercise?	**Yes**	**No**	**N/A**

15.	Did you do the **HEEL SLIDES **exercise?	**Yes**	**No**	**N/A**

16.	Did you do the **SIDE-LYING TO SIT **exercise?	**Yes**	**No**	**N/A**

17.	Did you do the **SITTING BALANCE **exercise?	**Yes**	**No**	**N/A**

18.	Did you do the **DYNAMIC SITTING BALANCE **exercise?	**Yes**	**No**	**N/A**

19.	OK.			

20.	**Exercises for ambulatory/able to stand independently:**			

21.	Did you do the **HIP AND KNEE BENDS **exercise?	**Yes**	**No**	**N/A**

22.	Did you do the **HEEL RAISES **exercise?	**Yes**	**No**	**N/A**

23.	Did you do the **SIT TO STAND **exercise?	**Yes**	**No**	**N/A**

24.	Did you do the **MARCHING IN PLACE **exercise?	**Yes**	**No**	**N/A**

25.	Did you do the **TANDEM WALKING **exercise?	**Yes**	**No**	**N/A**

26.	Did you do the **DYNAMIC STANDING BALANCE **exercise?	**Yes**	**No**	**N/A**

27.	OK.			

28.	What is preventing you from doing your **PRESCRIBED PHYSICAL ACTIVITIES?**	1. Not enough time to exercise		

		2. Not enough strength or energy		

		3. Do not understand how to do the exercise(s)		

		4. I need some help with the exercise(s)		

		5. Other:		

29.	What would make it easier for you to be active on a regular basis?	1. To make more time		

		2. Ask someone to explain how to do exercise(s)		

		3. Ask for help with exercise(s)		

		4. Other:		

30.	Do you still have trouble with balance activities?	**Yes**	**No**	**N/A**

31.	Do you still have trouble with strength activities?	**Yes**	**No**	**N/A**

32.	This is important for your recovery, well-being and overall health. Keep going.			

33.	Please review the set exercises that we have given you. These exercises will show you how to build back your strength.			

34.	Will you agree to do this?	**Yes**	**No**	**N/A**

35.	If answer is **NO**, "I'm sorry to hear that, but don't give up, keep trying during the next week."			

Telephone call visits 2-5 at Weeks 4, 6, 8 and 12 are directed towards reassessment and progression of the exercise program and the adaptive strategies, along with reviewing participant concerns pertaining to the toilet and tub/shower transfers and/or exercise adherence. The study protocol is designed to allow some flexibility in both the home visits with the assistant and the telephone calls with the teletherapist to enable the participant's most immediate needs to be addressed and to accommodate obtaining recommended adaptive equipment.

### Usual Care Group and Other Medical Care

Study participants randomized to Usual Care are informed that they will not get any extra care as part of the study. There are no attempts by study personnel to influence their self-care activities or physical functioning. The study's design ensures that both the TR and the Usual Care groups get any equivalent home health services that are provided as part of routine VA care, such as home health care by a nurse or nurse's aide, and/or visits by rehabilitation practitioners.

#### Telecommunication Technology

The study tried using several forms of technology to facilitate live two-way televisits between the teletherapist at the hospital and the participant and assistant in the home, including use of an analog videophone linked to a wireless transmitter and videocamera, and a wireless broadband internet system using a streaming Universal Serial Bus (USB) webcam linked to a VA encrypted laptop and virtual private network (VPN) to securely access the internet. However, the functionality of both systems for live two-way communication and capture of gross and fine motor function was erratic, so our protocol primarily relies on the videotaped recording of the session. The videocamera recording is very high quality and enables the teletherapist to assess fine motor movement and environmental characteristics. Depending on the assessment, the videocamera is either placed on an appropriately located tripod or hand carried by the assistant as the participant progresses through specific functional tasks. The assistants and teletherapists were all trained jointly in use of the technology, supplemented by detailed protocols already developed. Further, a training videotape was developed for new employees to view and for staff to use as a reference point of information.

#### In Home Messaging Device

The purpose of the IHMD is two-fold: to screen for unforeseen problems (i.e., allow for more efficient use of teletherapist time during the TR intervention) by identifying, a priori, potential issues or difficulties the study participant may be experiencing with recommended treatment and, to reinforce adherence to the recommended exercises. Due to its operability, the IHMD is employed only with those TR intervention participants who have an active analog telephone line in the home. The teletherapist views all the participant's answers via the Internet through software called the iCare Desktop. The IHMD uses standardized and validated scales targeting common post-stroke complications (depression, self-care/mobility, and falls) that might affect the success of the TR intervention or might be effectively treated by the TR.

Depression is common after stroke, occurring in approximately 25-40% of stroke survivors [24] and it can negatively affect patients' functional recovery and quality of life [25]. The IHMD uses the Patient Health Questionnaire (PHQ-9) [26] to screen for depression at baseline (Week 1-2) and 3-months. The PHQ-9 has been validated for telephonic administration [27] and its test-retest reliability [28] and predictive validity [29] are well characterized.

The IHMD screens for self-care/disability as recurrent disability is common after acute medical illness and hospitalization [30,31]. Moreover, frequent assessment of physical function is consistent with clinical practice in which therapists typically establish functional goals and monitor patient progress toward those goals. The IHMD automates some of this monitoring for the teletherapist. To assess the self-care/mobility, we use questions on lower extremity strength, self-care tasks, and mobility from the 16-item version of the Stroke Impact Scale (SIS-16) [32]. The SIS-16 is a psychometrically robust stroke-specific outcome measure and it has been validated for telephonic administration and its test-retest reliability is good [32]. Different questions are administered on different days to minimize participant burden, but all items are administered approximately every 2 weeks. If the participant screens positive, additional questions are used to determine whether this is a change over the preceding 2 weeks, the extent of the change, and if this is a change for the better or worse.

Once weekly, the IHMD screens for falls. Stroke patients have a four-fold increase in falls risk [33]. One study found that 73% of community dwelling stroke survivors reported falls [34]. Self-report of falls and near-falls on a daily or weekly basis has a long tradition of use in falls research [35]. The falls dialogue has three questions derived from previous research to determine if the participant has recently fallen or had a near fall, the number of times they might have fallen, and the scenario when they fell or almost fell (e.g., "unsteady when moving from bed to chair"; "bumped into things") [36]. Depending on the response, the teletherapist determines if the participant needs to be contacted prior to the next televisit and if the physician needs to be notified.

In addition to screening for depression, self-care/disability, and falls, the IHMD monitors exercise adherence, with the added advantage of providing instant feedback to the participant. For those reporting exercises at or near goal, the feedback is in the form of positive feedback and encouragement such as "You are doing a great job!". For participants recording exercises below goal, the IHMD ascertains the presence of potential barriers such as illness, pain, lack of energy or motivation. Appropriate messages that convey empathy with encouragement are delivered. A default option for report of not performing exercises is receipt of a personalized telephone call ("We are sorry you are having these difficulties, would you like the teletherapist to call you so that we can talk about them and try to get you back on track?").

#### Primary and Secondary Outcome Measures

Self-report instruments (surveys) are used to evaluate the primary and secondary outcome measures at baseline, 3-months and 6-months. Participants are administered the self-report instruments through telephone interviews executed by a research assistant located at the Coordinating Center, who is blinded to the study group assignment. Table 3 presents detailed descriptions of the self-report instruments used to answer the primary and secondary research questions. A brief description of each instrument follows. The motor subscale of the FONEFIM [6,7] is the primary outcome measure. There are four different instruments used to assess each of the four secondary research questions. The Late-Life Function and Disability Instrument [8] is a two-part instrument used to assess disability (altered performance of major life tasks and social roles) and functional limitations (altered ability to perform specific activities encountered in daily actions) [8,37]. The Falls Self Efficacy Scale [9] is used to measure the fear of falling. Reker et al.'s Stroke-Specific Patient Satisfaction with Care is used to measure the participants' satisfaction [10].

**Table 3 T3:** Study instruments used to measure the outcomes

1.	FONEFIM Motor subscale of the Telephone Version of the Functional Independence Measure
	The FONEFIM was developed as a telephonic alternative to the in-person, performance based Functional Independence Measure (FIM). It shows good concordance with the in-person FIM [6,7]. The FONEFIM instrument includes 18-items, each with a maximum rating of 7 (complete independence) and a minimum rating of 1 (complete dependence). Thirteen of the 18-items assess motor functioning encompassing four categories (FIM-motor): 1) self-care (e.g., bathing); 2) sphincter control (e.g., bladder management); 3) mobility (transfers to bed/chair/wheelchair); and 4) locomotion (e.g., walking). The motor subscale scores range from 13 to 91.

2.	**LLFDI** Late Life Function and Disability Instrument

	The LLFDI was developed as a comprehensive assessment of function and disability in community-dwelling older adults [8]. The disability component assesses self-reported limitation (capability) and frequency (performance) of engaging in 16 major life tasks. The functional construct evaluates self-reported difficulty in performing 32 physical activities, comprising three domains: upper extremity, basic lower extremity, and advanced lower extremity. The raw scores from each item response are transformed into linear scaled scores (0 to 100) and accordingly summed to represent component and domain values.

3.	**FES** Falls Self Efficacy Scales

	The FES is a 10-item scale that assesses the impact of fear of falling on a person's confidence to perform everyday tasks. An example of one of the items is: "How confident are you that you can take a bath or shower without falling?" Study participants rate each question on a scale of 0 to 10, and the scores are aggregated to give a total score between 0 (low fall-related self-efficacy) and 100 (high fall-related self-efficacy, that is very confident of not falling). The FES has good internal consistency (α = .91), test-retest reliability (r = .71), and construct validity [9].

4.	**SSPSC** Stroke Specific Patient Satisfaction with Care

	The SSPSC uses 15 items to assess three dimensions of satisfaction (nine items on hospital care, four items on home-based care, and two items on overall care) [10]. Each of the 15 items is scored using a Likert scale ranging from 1-4.

#### Control Variables

Sociodemographic variables (age, sex, race, education, income, marital status, and number of people living with the participant) are collected via self-report. Several clinical variables are collected at baseline as well. Stroke severity is measured by the Goldstein and Chilukuri scale, which is an algorithm to derive the Canadian Neurological Scale (CNS) retrospectively based on information in the patient's medical record [38]. The CNS, a highly reliable and valid stroke scoring system [39], focuses on level of consciousness, speech and strength. The aggregate physical dimension score from the Stroke Impact Scale (SIS) 2.0 is used at baseline to assess stroke related physical impairment [40]. The physical dimension score is a composite of four primary SIS domains: strength, hand function, ADL/IADL and mobility. The SIS uses a 5-point Likert scale ranging from "not difficult at all" to "cannot do at all." The Geriatric Depression Scale (GDS) is employed to measure depression [41]. The GDS is a 30-item scale, where each item is measured on a "yes/no" format. Scores range from 0 to 30, with higher values reflecting greater levels of depression.

#### Diary

Participants in both the TR and Usual Care groups track receipt of therapy services outside of the study intervention via a weekly diary for the entire three months of the intervention period. In this weekly diary, participants record receipt of physical or occupational therapy (yes or no). If yes, the participants are to include the time (in minutes) spent in receipt of therapy services, and the location of that therapy (VA hospital, VA outpatient facility, non-VA facility, and home). Participants are also asked if they have fallen or nearly fallen in their home, and the number of falls they experienced. The diary records whether or not they performed any study exercises (as prescribed by the teletherapist), or other exercises (those assigned outside of the study protocol), the number of minutes and number of times per day that they did so.

#### Exit Interview

Participants in the TR group are administered an exit interview after the 3-month outcome measure instruments have been completed. This interview is performed via telephone by the Coordinating Center. The interview includes 13 closed-ended questions using a 5-point Likert-type scale with different response options (e.g., "very unsatisfied" to "very satisfied"). The closed-ended questions assess the participant's view toward the **general intervention **(e.g., "How would you rate your overall satisfaction with the in-home intervention?"), **equipment **(e.g., "How comfortable were you being videotaped and then talking with the therapist?"), specific components of the **physical function component of the intervention **(e.g., "How useful was the toilet and tub/shower training for you?"), and **exercise component of the intervention **(e.g., "How often do you think you will apply what you learned from the exercise training in the future?"). In addition, there are four-open ended questions (e.g., "If you could change one thing about the whole intervention, what would it be?").

### Sample Size Determination and Statistical Power

The primary research question is: Over the study period, does the TR group have greater improvement in function (motor sub-scale of the FONEFIM) than the Usual Care group?

In our sample size calculations, we assume a standardized difference of 0.50 in the motor FIM score from baseline to 6 months, based on a randomized trial of a combination of assistive technology and exercise intervention similar to our study, that used a measure of ADL similar to the motor FIM over 6 months [42]. In a sample of 163 patients with a first ever stroke admitted for inpatient rehabilitation, Schepers et al. [42] reported a standard deviation of 8.3 for the unadjusted FIM motor domain for stroke patients. Based on a standard deviation adjusted to account for correlation between repeated measurements of the outcome, and using an independent samples t-test with a 0.05 two-sided significance level and 80% power, a sample size of 20 patients per group is required to detect a mean difference of 9.2 or higher in the FIM motor score between the intervention and control groups. Because we assume an approximate dropout rate of 20%, we are recruiting approximately 25 stroke patients per arm. We will test for baseline imbalances. If we find significant differences between the groups on baseline factors, we will control for these in secondary analyses to determine if these may account for between group differences in study outcomes.

If the proportion of drop outs are missing at random or missing completely at random, the likelihood-based mixed model for repeated measures will be applied for the data analysis. Multiple imputation techniques will also be applied to replace the missing data for both the cases that are considered to be drop outs and deaths. The results of the analyses using both the imputed and un-imputed data will be compared. If were to suspect that these analytical techniques were to yield missing not at random (MNAR) drop-out mechanisms or deaths, then we will try sensitivity analysis approaches based on the best scenario or worst scenario assumptions.

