**Methods:**

We describe an ongoing Phase II, 2-arm, 3-site randomized controlled trial (RCT) that determines primarily the effect of TR on physical function and secondarily the effect on disability, falls-related self-efficacy, and patient satisfaction. Fifty participants with a diagnosis of ischemic or hemorrhagic stroke will be randomly assigned to one of two groups: (a) TR; or (b) Usual Care. The TR intervention uses a combination of three videotaped visits and five telephone calls, an in-home messaging device, and additional telephonic contact as needed over a 3-month study period, to provide a progressive rehabilitative intervention with a treatment goal of safe functional mobility of the individual within an accessible home environment. Dependent variables will be measured at baseline, 3-, and 6-months and analyzed with a linear mixed-effects model across all time points.

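### The sample-size paragraph's four figures (standardized difference 0.50, SD 8.3, difference 9.2 points, 20 per group) cannot all be true, whatever correlation adjustment was applied to the SD

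*Protocol article*

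**What the plan says.** All the sizing inputs are in the Protocol article, under Sample Size Determination and Statistical Power, and concern the primary outcome.

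- Assumed effect: "we assume a standardized difference of 0.50 in the motor FIM score from baseline to 6 months".
- SD: a cited stroke cohort "reported a standard deviation of 8.3 for the unadjusted FIM motor domain for stroke patients".
- Adjustment: "Based on a standard deviation adjusted to account for correlation between repeated measurements of the outcome". Neither the adjusted SD nor the correlation is printed.
- Test: "using an independent samples t-test with a 0.05 two-sided significance level and 80% power".
- Result: "a sample size of 20 patients per group is required to detect a mean difference of 9.2 or higher in the FIM motor score".
- Dropout: "Because we assume an approximate dropout rate of 20%, we are recruiting approximately 25 stroke patients per arm".

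The Methods part of the Abstract gives the matching total of fifty participants.

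**The concern.** A reader will take the 0.50 to be the effect for which the trial was sized, because it opens the calculation as its assumption. Twenty per group is far fewer than a two-sample t-test needs for an effect of that size on its own scale, and 9.2 points is more than half of the only SD printed.

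This paragraph is the sole justification for the sample of 50. If it is taken to mean 80% power for a moderate effect, a null result could be read as evidence against an effect that the trial may have had little chance of detecting.

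**Working it through.** **Inputs** (all from the sample-size section): d = 0.50; unadjusted SD = 8.3; difference = 9.2 points; n = 20 per group; two-sided alpha 0.05; power 80%; independent-samples t-test; dropout 20%. The correlation rho is not given, so it is varied below as an assumption. Power is from the noncentral t distribution.

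**1. Can 20 per group be reproduced?**
- From d = 0.50: n = 63.8, so 64 per group (63 by the normal approximation; 50.2 before rounding if one-sided).
- From 9.2 points and the unadjusted SD: d = 9.2 / 8.3 = 1.11, n = 13.8, so 14 per group.
- Neither gives 20. The dropout step does reproduce: 20 / 0.8 = 25 per arm, 50 in total.

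**2. What does 20 per group imply?**
- 80% power at n = 20 per group requires d = 0.909.
- With 9.2 points, the SD entering the test is 9.2 / 0.909 = 10.12. The article does not print this figure.

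**3. Can 8.3 become 10.1?**
- As a change score, SD x sqrt(2(1 - rho)): (10.12 / 8.3)^2 = 1.487 = 2(1 - rho), so rho = 0.26.
- As a baseline-adjusted analysis, SD x sqrt(1 - rho^2): never, since this factor cannot exceed 1.
- Other variance factors are conceivable: 1 + rho = 1.487 gives rho = 0.49, and 1 + 2rho = 1.487 gives rho = 0.24.
- So 8.3, 9.2 and 20 per group can be made to agree under some assumed adjustments.

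**4. Can 0.50 then also hold?** If 0.50 and 9.2 points describe the same effect:
- in units of the working SD, 9.2 / 10.12 = 0.91, not 0.50;
- in units of the unadjusted SD, 9.2 / 8.3 = 1.11, not 0.50.

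This does not depend on the form of the adjustment. For 9.2 points to be 0.50 SD, the SD must be 9.2 / 0.50 = 18.4.

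If they are different effects, 0.50 is 0.50 x 10.12 = 5.06 points or 0.50 x 8.3 = 4.15 points. Both lie well below the 9.2 points to which the 80% power is attached.

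**5. Power for 0.50**

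*If 0.50 is in units of the SD in the t-test:* 33.8% with 20 per arm and 41.0% with 25. Reaching 80% takes 64 evaluable per arm, or 64 / 0.8 = 80 recruited.

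*If 0.50 is in units of the unadjusted SD*, power with 20 per arm depends on rho:

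| rho (assumed) | Change score | Baseline-adjusted |
|---|---|---|
| 0 | 19% | 34% |
| 0.5 | 34% | 43% |
| 0.8 | 68% | 73% |
| 0.9 | 93% | 94% |

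- 80% is reached at rho of about 0.85 (change score) or 0.84 (baseline-adjusted).
- With SD 8.3 and a change-score rho of 0.85, the working SD is 8.3 x sqrt(0.30) = 4.55 and the detectable difference is 0.909 x 4.55 = 4.1 points, not 9.2.
- Keeping the working SD of 10.12 that 9.2 implies, d = 4.15 / 10.12 = 0.41 and power is 24%.

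**The case against.** **The adjusted SD.** The article says that the SD was adjusted for correlation, so testing 9.2 points against the raw 8.3 does not test the stated calculation. That is right. The 14 per group in step 1 (or the 93% power that 20 per group would give at 1.11 SD) does not show that the trial is larger than it needs to be. It shows only that 8.3 cannot be the SD in the test. With rho = 0.25 in a change score, the SD is 8.3 x sqrt(1.5) = 10.17 and the detectable difference 9.24 points. The sizing sentence may therefore be sound on its own, leaving the 0.50 clause as the misfit.

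**The misfit may be elsewhere.** If the unadjusted SD were 18.4 and the correlation about 0.84 to 0.85, then 0.50, 9.2 and 20 per group would agree and only 8.3 would be wrong. This also stands. It saves three figures by giving up the only SD printed, so it confirms the contradiction rather than removing it.

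**The 80% is attached to 9.2 points.** The text does not say in so many words that 20 per group detects 0.50. True, but 0.50 is introduced as the assumption of the calculation, and the reader is given no other role for it.

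**An article may leave details to the full protocol.** Agreed: leaving out the adjusted SD and the correlation is not a fault in itself. The point is that no value of either reconciles the figures that are printed.

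**The mixed model.** The Primary Analyses section plans a linear mixed-effects model, which may be more efficient than a t-test. The stated sizing is nevertheless a t-test, and that section supplies no figure that resolves the conflict.

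**Conclusion.** The paragraph is wrong as written. No correlation-adjusted SD makes 0.50, 8.3, 9.2 points and 20 per group at 80% power all true. This needs only the stated test, alpha and power, and the natural reading that 0.50 and 9.2 describe the same planning effect.

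The firm result is that 20 evaluable per arm gives 80% power for 0.91 SD on the analysis scale, 1.8 times the stated 0.50 if that is the scale meant (0.909 / 0.50).

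A reader might go further and infer that the trial simply has 34% power instead of 80%. The document does not support this as a flat statement. The 34% and the 64 per arm hold if 0.50 is in units of the SD in the t-test. In units of the unadjusted SD, a change-score analysis gives from 19% at rho = 0 to 80% at rho of about 0.85. It gives 24% if the working SD implied by 9.2 is kept.

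Nor can one conclude that the authors used an SD of 10.1 and a correlation of 0.26. The SD is back-calculated from 9.2 and 20 per group, and the correlation rests in addition on one assumed form of adjustment.

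**What to change.** Rewrite the paragraph so that its figures agree:

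1. Say which SD the 0.50 refers to.
2. Give the adjusted SD, the correlation and the form of adjustment actually used.
3. Correct or remove whichever of 0.50, 8.3 or 9.2 did not enter the calculation. The authors must identify it from their records; it cannot be settled from the article.
4. State that 20 evaluable per arm gives 80% power for about 0.91 SD on the analysis scale, and report the power for 0.50 that follows.
5. Optionally, add the detectable difference by assumed correlation. With SD 8.3, a change score and 20 per arm, 0.909 x 8.3 x sqrt(2(1 - rho)) gives 8.9 points at rho = 0.3, 7.5 at 0.5 and 5.8 at 0.7.

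The cost is one paragraph of rewording, with no added patients and no change to the design. The stated sensitivity of the trial may become less favourable.

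### Motor scores are imputed after death as if the participant had dropped out, and the only check on informative dropout is triggered by suspicion and left undefined

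*Protocol article*

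**What the plan says.** The missing-data plan is the last paragraph of Sample Size Determination and Statistical Power in the protocol article. It has four steps.

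- A condition on the main model: "If the proportion of drop outs are missing at random or missing completely at random, the likelihood-based mixed model for repeated measures will be applied".
- Imputation, with deaths and dropouts treated alike: "Multiple imputation techniques will also be applied to replace the missing data for both the cases that are considered to be drop outs and deaths".
- A comparison of the results with and without imputation.
- A fallback, used if the team comes to suspect that dropout or death is MNAR: "we will try sensitivity analysis approaches based on the best scenario or worst scenario assumptions". The scenarios are not defined, and no rule says when suspicion is strong enough.

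The next section, Primary Analyses, names a linear mixed-effects model for the motor FONEFIM at baseline, 3 and 6 months, by intention to treat, with no condition on the missing-data mechanism. Table 3 gives the scale: "The motor subscale scores range from 13 to 91". Death is listed among the potential harms to be reviewed (under Secondary Analyses), but no expected rate is given and no score or composite is assigned to a participant who dies.

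**The concern.** **Deaths.** Imputation is meant to recover a value that exists but was not observed. After death there is no motor function to observe. An imputation model built on participants with observed scores gives the dead person the score that a comparable survivor would have had. The mixed model does much the same without showing it, because it extrapolates each person's course under MAR. If deaths differed between arms, both analyses would describe a population in which nobody dies, and neither would show that the result depended on this.

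**Informative dropout.** The two analyses that are set against each other, standard multiple imputation and the likelihood model, both assume MAR. Their agreement does not support MAR and their disagreement does not diagnose MNAR. The trigger for the MNAR work therefore cannot operate as described. Whether that work is done, and in what form, becomes a decision taken after the data are seen.

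**Conflicting wording.** One section makes the mixed model conditional on a mechanism that observed data cannot verify. The next adopts it outright.

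**Working it through.** **Inputs from the protocol article.** Scale limits 13 and 91, so a range of 91 - 13 = 78. For the target difference and evaluable number: "a sample size of 20 patients per group is required to detect a mean difference of 9.2 or higher in the FIM motor score". Dropout is about 20%, with about 25 recruited per arm. The SD is 8.3, stated as unadjusted; the adjusted SD is not given.

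**The plan's own figure.** 20 / (1 - 0.20) = 25 per arm, as stated. The planned amount of missing data is therefore 5 of 25 per arm.

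**Best and worst case at the scale limits.** Assume the same missing share m in both arms and a completer difference of 9.2. Set missing values to 91 in one arm and 13 in the other, then reverse. The difference in means is

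(1 - m) × 9.2 ± m × 78

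| Missing per arm | m | Calculation | Range |
|---|---|---|---|
| 5 | 0.20 | 7.36 ± 15.60 | -8.2 to 23.0 |
| 3 | 0.12 | 8.10 ± 9.36 | -1.3 to 17.5 |
| 2 | 0.08 | 8.46 ± 6.24 | 2.2 to 14.7 |
| 1 | 0.04 | 8.83 ± 3.12 | 5.7 to 12.0 |

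At the planned dropout the width is 2 × 15.6 = 31.2 points, which is 31.2 / 9.2 = 3.4 times the target. The lower bound reaches zero when 9.2(1 - m) = 78m, so m = 9.2 / 87.2 = 10.6%, or between two and three missing per arm.

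**A milder reading.** Set missing values to the arm mean plus or minus k SD, at 20% missing. The range is 9.2 ± 0.20 × 2 × k × SD.

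- k = 1, SD 8.3: 9.2 ± 3.32, or 5.9 to 12.5.
- k = 1, SD 10.1: 9.2 ± 4.04, or 5.2 to 13.2.
- k = 2, SD 8.3: 9.2 ± 6.64, or 2.6 to 15.8.
- k = 2, SD 10.1: 9.2 ± 8.08, or 1.1 to 17.3.

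The SD of 10.1 is the value at which 20 per group gives 80% power for 9.2 points (detectable standardised difference 0.909; 9.2 / 0.909 = 10.1). All these ranges are for the point estimate and leave out sampling error.

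**One death.** Replace an imputed score s by the scale minimum in an arm of 25: the mean moves by (s - 13) / 25. The imputed score is an assumption, so a range is shown.

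- s = 50: 37 / 25 = 1.5 points.
- s = 70: 57 / 25 = 2.3 points.
- s = 85: 72 / 25 = 2.9 points.

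Against the 9.2-point target this is 16% to 31% for each death.

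**The case against.** **The primary method is already fixed.** A reader might infer from the conditional wording that the primary method could be chosen after seeing the data. The document does not support that. Primary Analyses names the mixed model without condition, no rival primary method appears anywhere, and the MNAR step is called a sensitivity analysis. What stands is that the two sections conflict.

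**The fallback is not always too wide.** A reader might infer that best/worst-case analysis can never inform the result. That holds only if the scenarios are the scale limits and dropout is near the planned level. With two or fewer missing per arm, or with the SD-based scenarios above, the range stays above zero. An article may leave the definitions to a fuller document. The suspicion trigger, however, is a stated rule and not an omitted detail.

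**The fallback also covers deaths.** It does, and a worst scenario could turn out to be a lowest-score analysis. But it is contingent, and nothing says so.

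**The two MAR analyses need not agree.** True: the imputation model could use variables that are not in the mixed model, such as the depression score or the diary data. A difference would then reflect those variables and would still not establish MNAR. Imputation can also condition on a participant's own earlier scores, so it need not give the dead an average value. It would still be a survivor's value.

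**The size for deaths is hypothetical.** No death rate is given, and the 1.5 to 2.9 points is the gap between two scoring conventions. It should not be read as an estimate of bias.

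**Conclusion.** The point holds in this form. The plan states that deaths are imputed like dropouts, and neither the imputed analysis nor the mixed model handles death. Its MNAR work depends on a suspicion that the planned comparison cannot establish, and it uses undefined scenarios. On the scale-limit reading at 5 of 25 missing per arm, that work would return a range of -8.2 to +23.0 around a completer difference of 9.2, which is uninformative. This assumes equal missingness in both arms and ignores sampling error. One death can shift an arm mean by 1.5 to 2.9 points between conventions, for assumed imputed scores of 50 to 85. In a trial of about 50 participants that is enough to need a stated rule. The named primary model is not in question; the safeguards around it are.

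**What to change.** 1. Delete the MAR/MCAR condition under Sample Size Determination and Statistical Power, so that the mixed model is primary without condition, as under Primary Analyses.
2. Restrict multiple imputation to dropouts and leave outcomes after death unimputed. This alone changes little, because the mixed model still extrapolates past death, so item 3 is needed as well.
3. Prespecify one sensitivity analysis in which deaths take the lowest score (13) or the lowest rank.
4. Replace the suspicion-triggered best/worst case with a delta-adjusted (tipping-point) imputation for dropouts that is always run, with shifts up to about the 9.2-point target. If the full shift were applied to 5 TR dropouts of 25, the TR mean would move by 5 × 9.2 / 25 = 1.8 points, a range that can be interpreted.

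The cost is a change of wording and a little more analysis work. No new data or participants are needed, and the primary model stays as it is.
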